##### PRWIMT protocol

The PRWIMT protocol consists of conventional PR as previously described. Individuals will also perform a placebo IMT using a POWERbreathe® device (POWERbreathe International Ltd., Southam, UK) without any load for 3 cycles of 12 repetitions.

##### PRIMTLL protocol

The PRIMTLL protocol consists of conventional PR and the use of POWERbreathe®. POWERbreathe KH1 (POWERbreathe International Ltd.) will be used for IMT. This equipment is based on resistance training to inspiration and consists of a mouthpiece coupled to the equipment, which will electronically generate inspiratory resistance to the exercise. POWERbreathe KH1 performs an automatic estimate of the patient’s load necessity at the beginning of each session [21]. Respiratory muscle training will be performed using 35% of maximal inspiratory pressure (MIP), increasing 5% every week until reaching 80% of MIP at the 10th week, which will be maintained until the end of the protocol. The MIP will be accessed weekly to adjust the training load percentage. Subjects will perform 3 cycles of 12 repetitions as proposed by Huang et al. [22].

##### PRIMTIVH protocol

The PRIMTIVH protocol consists of conventional PR and IMT using an STMedical® device (SpiroTiger, Chamonix Mont Blanc, France). Respiratory muscle training in voluntary isocapnic hyperventilation mode will be performed with the STMedical® device Pulmonary Rehabilitation Maximal Voluntary Hyperpnea (PRMVH), consisting of a portable unit with a pouch and a base station. A two-way piston valve is connected to a rebreathing bag, which maintains a constant isocapnic fraction of carbon dioxide [23]. Individuals will receive training with duration up to 20 min, one minute of training and one minute of rest, where they will be encouraged with instructions such as “breathe faster.” The training respiratory rate chosen will be calculated as 35-fold forced expiratory volume in the first second (FEV_1_), so that ventilation corresponds to 50–60% of maximal voluntary ventilation (MVV) [24]. They will start with a respiratory rate (RR) between 26 and 30 bpm lasting for 1 min, until completion of 20 min of training with the target RR. The volume of the rebreathing bag will be based on the forced vital capacity (FVC) of the patient, starting with a rebreathing bag size approximately equivalent to 50–60% of the FVC [25, 26].

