#### Lung function test

Lung function will be assessed using a KoKo DigiDoser spirometer (Nspire Health, Longmont, CO, USA). Technical procedures, acceptability, and reproducibility will follow the recommendations of the American Thoracic Society/European Respiratory Society (ATS/ERS) [28]. Subjects will perform between three to eight maneuvers, and the best three will be recorded with variability less than 5% or 200 ml. The test will be performed before and after the use of an inhalation bronchodilator. Absolute and predicted values of FEV_1_, FVC, and FEV_1_/FVC will be considered and analyzed using a previously published equation for the study population [29].

The dynamic muscular endurance test (MVV) will also be performed. The dynamic test will be performed by MVV during 15 s (MVV_15s_) using a KoKo DigiDoser spirometer (Nspire Health). The individual will be positioned in a seated position on a bench with a nose clip and will be instructed before the beginning of the test to “breathe as fast and deep as possible.” During the test, active stimulation will be carried out with the cadence “pull and drop, pull and drop” to maintain a constant and regular rhythm with the same volume and frequency during the whole test. The maneuver will be assessed by three tests of 15 s. The highest value will be considered the best test. A difference less than 10% among the tests will be set [28, 29].

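### Hyperpnoea arm: a training rate of 35 × FEV1 does not deliver the stated 50–60% of MVV at ordinary FVC if each breath is about one starting bag

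*Protocol article*

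**What the plan says.** The section on the PRIMTIVH protocol links three quantities.

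- Rate: "The training respiratory rate chosen will be calculated as 35-fold forced expiratory volume in the first second".
- Intensity, given in the same sentence as the result of that rate: "so that ventilation corresponds to 50–60% of maximal voluntary ventilation (MVV".
- Bag: its volume is tied to each patient's FVC. For the opening size the text has "starting with a rebreathing bag size approximately equivalent to 50–60% of the FVC".

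It also gives an opening rate, "They will start with a respiratory rate (RR) between 26 and 30 bpm lasting for 1 min", and then continues "until completion of 20 min of training with the target RR".

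MVV is measured in every patient. Under Lung function test: "The dynamic test will be performed by MVV during 15 s (MVV_15s_) using a KoKo DigiDoser spirometer". The article gives no MVV-to-FEV1 ratio, no units for the 35-fold product and no spirometric values for the intended patients.

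**The concern.** Ventilation is rate times breath volume. The rate here depends on FEV1 only, and the bag depends on FVC only. Their product therefore carries an FVC term that the stated share of MVV does not have. One constant is then unlikely to give 50–60% of MVV in patients whose lung volumes differ.

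What is at stake is the training dose in one of the two experimental arms. The trial is meant to show which form of inspiratory muscle training to add to rehabilitation. A therapist who applied the written rule would, at larger FVC, ask for ventilation well above the intended intensity. A therapist who did something else would deliver a dose that the article does not describe.

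**Working it through.** **Inputs from the article (PRIMTIVH protocol).** Rate = 35 × FEV1 per minute. Bag fraction b = 0.5–0.6 of FVC. Target t = 0.5–0.6 of MVV.

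**Assumptions, not in the article.** Breath volume is about one starting bag. MVV = k × FEV1, with k = 30–45. The patient volumes below are illustrative.

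**Formula.** Ventilation = 35 × FEV1 × b × FVC. As a share of MVV this is 35 × FEV1 × b × FVC / (k × FEV1) = (35/k) × b × FVC. FEV1 cancels and FVC stays.

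**1. When the stated figure is reproduced.** With k = 35 and FVC 1.0 L the share equals b, which is 50–60%. In general the target is met when FVC = (k/35) × (t/b), and t/b runs from 0.5/0.6 = 0.833 to 0.6/0.5 = 1.20.

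- k = 30: 0.71–1.03 L
- k = 35: 0.83–1.20 L
- k = 40: 0.95–1.37 L
- k = 45: 1.07–1.54 L

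Agreement is therefore confined to FVC of about 0.7–1.5 L. For any single k the window spans 1.20/0.833 = 1.44-fold.

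**2. A worked patient: FEV1 1.2 L, FVC 2.4 L.** Rate = 35 × 1.2 = 42/min. Bag = 0.5–0.6 × 2.4 = 1.20–1.44 L. Ventilation = 42 × 1.20 to 42 × 1.44 = 50–60 L/min. MVV = 30–45 × 1.2 = 36–54 L/min. The share is 50.4/54 to 60.5/36 = 93–168%, or 105–144% with k = 35–40.

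**3. Other FVC values, k = 30–45.**

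- FVC 1.2 L: 47–84% of MVV
- FVC 1.8 L: 70–126%
- FVC 3.2 L: 124–224%

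**4. Without choosing k.** The rule holds only if MVV/FEV1 = 35 × (b/t) × FVC = 29.2–42.0 × FVC. At FVC 2.4 L that is 70–101, or an MVV of 84–121 L/min at FEV1 1.2 L. As a yardstick, exhaling for a whole minute at the mean flow of the first second, with no time to inhale, gives 60 × FEV1.

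**5. Spread between patients.** Take two patients with equal FEV1 and MVV and the same bag fraction, but FVC 1.8 and 3.2 L. They get the same rate and ventilations 3.2/1.8 = 1.78-fold apart. The target band is 0.6/0.5 = 1.2-fold wide, so both cannot lie inside it.

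**6. The product read as a ventilation in L/min.** 35 × FEV1 is 50–60% of MVV only if MVV = 35/0.6 to 35/0.5 = 58–70 × FEV1. With k = 30–45 it is 35/45 to 35/30 = 78–117% of MVV. Changing the unit alone does not rescue the sentence.

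**7. Starting rate.** Read literally, the target rate falls below 26/min when FEV1 is under 26/35 = 0.74 L. If the rate is instead derived from the 50–60% target at one bag per breath, it is (t/b) × k × FEV1/FVC. With k = 35–40 that is 14.6–24.0/min at FEV1/FVC 0.50 and 19.0–31.2/min at 0.65. In some patients it is below the stated start of 26–30/min.

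**The case against.** The strongest reply is that the article never equates a breath with a bag. It calls the bag size approximate and a starting value. This stands, and it is why the point is conditional: a reader might infer that the three rules contradict each other outright, and the text does not support that. The condition is not easily escaped, however. Breaths larger than the bag widen the gap. Smaller breaths close it only if they are t × k/35 = 0.43–0.77 L (k = 30–45), a volume that does not depend on FVC and so sits oddly with a bag sized to FVC.

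A reader might also infer that the sentence is shown to be a ventilation mislabelled as a rate. That is possible but not established. The article gives no unit, the reference cited for the sentence is not at hand, and a rate reading is not absurd: it gives 26–30/min at FEV1 0.74–0.86 L (26/35 to 30/35).

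Nor can one conclude that patients will be over-ventilated. The article does not show whether therapists will follow the formula literally, and the percentages come from assumed volumes and ratios.

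The lack of a rule for changing the bag later is operating detail that an article may leave to the full protocol. It is not part of this point.

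Finally, the intended intensity is explicit and MVV is measured, so the aim can be recovered. That makes the repair cheap. It does not make the written rule correct, because the sentence gives both a formula and its result, and at ordinary FVC the two disagree under the stated condition.

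**Conclusion.** The point holds in conditional form and should be corrected. If breath volume is about the starting bag, a rate of 35 × FEV1 does not give 50–60% of MVV at ordinary FVC. At FVC 2.4 L it would need MVV of 70–101 × FEV1, and with an assumed MVV of 30–45 × FEV1 it gives about 93–168%. Agreement is limited to FVC of about 0.7–1.5 L under that same range.

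Confidence is high that, under this condition, the rate, bag and intensity rules do not agree across patients. It is low to moderate for the percentages, which are illustrations. The effect is on the dose and reproducibility of the PRIMTIVH arm. Sample size and error rates are unaffected.

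**What to change.** Let the stated intensity govern.

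1. Set target ventilation at 50–60% of each patient's measured MVV.
2. Calculate the respiratory rate as target ventilation divided by the actual breath volume on the device. Use bag volume as the divisor only if one breath is about one bag.
3. Delete 35-fold FEV1 as a rate, or correct it against its cited source and give its units.
4. Check that the 26–30/min starting rate does not exceed the resulting target rate in each patient.

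The cost is one or two sentences and the therapist worksheet. MVV and FVC are already measured. The only possible addition is a reading of breath volume during training, if it differs from the bag.

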### Outcome measures

#### Anthropometric assessment

Patients will be assessed for their height and body weight through an anthropometric scale coupled with a Filizola stadiometer (Filizola PL200®, São Paulo, Brazil) and a maximum capacity of 200 kg in order to calculate body mass index (BMI). As proposed by Quetelet (1835), BMI has been used by the World Health Organization (WHO) since 1997 as a reference measure of obesity worldwide and is expressed as the weight in kilograms divided by the square of the height in meters (weight/height^2^) [27].

#### Lung function test

Lung function will be assessed using a KoKo DigiDoser spirometer (Nspire Health, Longmont, CO, USA). Technical procedures, acceptability, and reproducibility will follow the recommendations of the American Thoracic Society/European Respiratory Society (ATS/ERS) [28]. Subjects will perform between three to eight maneuvers, and the best three will be recorded with variability less than 5% or 200 ml. The test will be performed before and after the use of an inhalation bronchodilator. Absolute and predicted values of FEV_1_, FVC, and FEV_1_/FVC will be considered and analyzed using a previously published equation for the study population [29].

The dynamic muscular endurance test (MVV) will also be performed. The dynamic test will be performed by MVV during 15 s (MVV_15s_) using a KoKo DigiDoser spirometer (Nspire Health). The individual will be positioned in a seated position on a bench with a nose clip and will be instructed before the beginning of the test to “breathe as fast and deep as possible.” During the test, active stimulation will be carried out with the cadence “pull and drop, pull and drop” to maintain a constant and regular rhythm with the same volume and frequency during the whole test. The maneuver will be assessed by three tests of 15 s. The highest value will be considered the best test. A difference less than 10% among the tests will be set [28, 29].

#### Maximal respiratory pressure, sniff nasal inspiratory pressure (SNIP), and sustained maximum inspiratory pressure (SPImax)

Respiratory muscle strength will be measured using a MicroRPM digital manometer (NEPEB-LabCare/UFMG, produced in Belo Horizonte, Brazil). Technical procedures, acceptability, and reproducibility will follow the recommendations of the ATS/ERS (2002) [30]. To obtain MIP, the individual will be instructed to perform one maximal expiration (close to residual volume, RV) followed by a maximal inspiration (close to total lung capacity, TLC). To obtain maximal expiratory capacity (MEP), the individual will be instructed to perform a maximal inspiration (close to TLC) followed by a maximal expiration (close to RV) [31]. A maximum of five maneuvers will be performed for each evaluation, and the highest value will be considered so that the difference among the maneuvers does not exceed 10% among the best three tests. Obtained values will be compared to reference values for the Brazilian population [32].

The SNIP, or sniff, test will be performed with one nostril occluded by a nose clip connected to the manometer through a catheter measuring approximately 1 mm. The maneuver will be performed from functional residual capacity (FRC). The individual will be instructed to perform a slow sustained expiration followed by a maximal sniff (inspiration) through the contralateral nostril. All subjects will perform 10 maneuvers with a 30-s interval among them [33]. The highest maneuver will be compared to previously described equations to determine reference values for the studied population [34].

To measure SPImax, the same manometer will be used. The manometer will be connected to a diver through an acrylic piece with an air leak orifice of 2 mm and a 6-mm occlusion orifice. The manometer will communicate with software (Manovac 3.0-A), whereby the data will be accessed after being collected [35–37]. Individuals will be instructed to breathe quietly close to tidal volume through the nozzle connected to the manometer for three consecutive breaths. The evaluator will give the following verbal command: “Push the air out, push the air into ... ”. The next steps are as follows: (1) slow exhalation, close to the residual volume at the verbal command “Push all the air out ... ”; (2) signaling the end of the total and slow exhalation by the patient, shown by raising the left arm; (3) obstruction of the occlusion hole by the evaluator, and (4) achieving a maximum inspiratory effort, near to total lung capacity, which will be sustained as long as possible, at the command: “Take a deep breath! And hold it, hold it ... ... ... hold it” [30, 37, 38]. The test will be considered complete when the subject performs at least three acceptable efforts, which means with no air leakage between the lips and the mouthpiece and/or nose clip, and of these, two reproducible efforts (with variation equal to or less than 10% of the test, with the variable area under the pressure-time curve value, since it was not the last test). Up to eight inspiratory efforts will be performed, with a one-minute interval between the tests [39].

#### Assessment of chest wall volumes

Analysis of respiratory kinematics integrated to signals of lung volumes, flow, pressure, and respiratory muscle activity will be assessed during a spirogram (one minute of quiet breathing [QB] followed by a maximum respiratory cycle, 20 s of QB, a maximum voluntary ventilation for 15 s, and one minute of QB). All signals will be integrated using Optoelectronic Plethysmography (OEP) System; BTS, Milan, Italy). The evaluation of flow and pressure generated in the airways will be performed using a Series 0–800 lpm pneumotachograph (flow measurement head), interconnected to a Series RSS100HR amplifier (Research Pneumotach System, Hans Rudolph, Inc.; Shawnee, KS, USA). The chest wall volumes and its compartments (rib cage pulmonary, rib cage abdominal, and abdomen) will be assessed by OEP System. This system allows the computational kinematic analysis of the three dimensions of the chest wall complex through 89 optical sensors placed on the chest wall. The sensors, small hemispheres (5 mm in diameter) coated with a reflective substance, will be circumferentially placed on the three horizontal regions of the chest wall between the collarbone and the superior iliac spine. Sensors will be placed in five vertical columns on the anterior and posterior regions and in two additional columns on the axillary line [40–43]. The limit between the pulmonary and abdominal rib cage will be assumed at the xiphoid process level, and the limit between the abdominal rib cage and abdomen will be assumed as the lower anterior costal margin and lower posterior costal margin. Coordinates of the sensors will be assessed by using a kinematic configuration system in eight photosensitive cameras (four on the front region and four on the back region) with an acquisition frequency of 60 Hz. Based on the captured images, the volumes of the chest wall will be computed by a triangulation surface. Respiratory pattern volume, flow, and time will be considered for the analysis. Additionally, operational volumes (end inspiratory volume and end expiratory volume) will be evaluated [44].

#### Peripheral muscle strength

Upper limb muscle strength will be obtained by hand dynamometry on the dominant side using Jamar equipment (Sammons Preston, Bolingbrook, IL, USA). Three reproducible tests will be performed (≤ 5%), and the highest obtained value will be considered for analysis using a previously described reference equation [45]. Lower limb muscle strength will be assessed using the maximal repetition (MR) test of the dominant limb on an extension board (405 Embreex Physicus, Brazil) with a load capacity of 50 kg [46].

#### Six-Minute Walk Test (6MWT) and Incremental Shuttle Walking Test (ISWT)

The 6MWT will be performed following the technical procedures described by the ATS [47]. Respiratory rate, heart rate, and peripheral oxygen saturation (SpO_2_) by portable pulse oximeter (Nonim Medical, Inc., 2500A, Plymouth, MN, USA) and systemic arterial pressure (SAP) using an analogue tensiometer (Becton Dickinson - BD®, Brazil) and a stethoscope (Littmann® classic II, 3M, Saint Paul, MN, USA) will be assessed before, immediately after, and 2 min after the end of the test. The subjective symptoms of dyspnea and fatigue of lower limbs will be evaluated with the modified Borg scale, from 0 to 10 [14]. Heart rate and SpO_2_ will be monitored every minute during the test. At the end of the test, the total distance walked will be calculated, and the equation of Iwama et al. [48] will be used to calculate the predicted walking distance during the test. To evaluate the maximum work (Wmax) performed during the 6MWT, the equation proposed by Hill et al. [49], which is based on the subject’s body weight, will be used. The predicted values of distance will be calculated according to Iwama et al. [48].

The ISWT will be performed according to Singh et al. [50]. The test will be interrupted by subject exhaustion or if the individual is not able to keep the proposed speed. Respiratory and cardiac frequency, SpO_2_, SAP, and subjective symptoms of dyspnea and lower limb fatigue will be measured before and after the test with the modified Borg scale [14, 51]. The equation of Probst et al. [52] will be used to calculate predictive walking distance in the study.

#### Dyspnea and health status

Perceived dyspnea will be evaluated by the modified Medical Research Council (mMRC) scale, which has five different items in which the subject chooses the one that corresponds to the limitation caused by dyspnea in their activities of daily living (ADL) [53].

The Chronic Obstructive Pulmonary Disease (COPD) Assessment Test (CAT) aims to determine the impact of COPD on health status [54]. This questionnaire is simple and easy to apply, consisting of 8 questions about general symptoms and limitation in ADL. The score varies from 0 to 5 points in each item, totaling a maximum of 40 points, and this score has been included in the new classification of patients with COPD, to direct medication treatment and define mortality risk. Lower scores correspond to a low impact of the disease on health status and scores above 10 are representative of patients with higher risk, with poorer health status due to COPD [1]. The Portuguese version will be used, validated for the Brazilian population [55].

#### Sample size

The sample size was calculated using two-way analysis of variance (ANOVA) for repeated measures by analyzing walking distance and the standard deviation in meters on the 6MWT from previously published data [15]. A two-tailed alpha error of 0.01 was implemented with a power of 95%, considering clinical improvement for COPD patients after PR and a difference of 30 m between groups on the walking test. For the calculations, the following means and standard deviations of the time observed in the 6MWT in the rehabilitation and control groups were used: pre-PR 312.43 ± 51.26 and post-PR 342.85 ± 48.82 m (rehabilitation group); pre-PR 305.13 ± 54.60 and post-PR 298.20 ± 52.81 m (control group), and a sample size of 32 subjects was found (effect size = 1.04). As the study of Elci et al. [15] was composed of two groups (rehabilitation and controls) and ours will be composed of three groups, we will assume that the 32 subjects will be part of the rehabilitation program (the PRIMTLL and PRIMTIVH groups), and 16 more subjects will be added as a study control group for a total sample of 48 subjects. In addition, 12 more subjects will be added into the study, because we will also assume a 20% loss to follow-up as well as 5% missing data, for a total sample size of 60 subjects.

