All three groups will submit to a conventional rehabilitation program consisting of aerobic exercise on a treadmill. For the first week, the subjects will perform 20 min of activity. A resting period lasting 2 min maximum will be allowed whenever requested by the subject. The training time will be increased after the 5th week to reach 30 min of daily activity [15]. Aerobic exercise will be performed on a treadmill, with a velocity corresponding to 70% of the maximum velocity achieved in the Incremental Shuttle Walking Test (ISWT) [16]. Ten percent of the starting time (2–3 min) of the training will be at a speed of 40% of the maximum speed reached in the ISWT for heating, 80% of the training time (17–25 min) will be at the target speed (70% ISWT), and the remaining 10% of the time will be cooling, with the same speed as for heating, reducing the speed to zero at the end of the training period [17, 18]. The physical activity training will be interrupted whenever the degree of dyspnea sensation reaches 4–6 (intense) on the Borg scale [14] or the heart rate (HR) exceeds 85% of the individual maximum HR value (220 – age). If the saturation drops (SpO_2_ < 90%) [19] during the exercise, we will administer supplemental oxygen at minimal flow with a nasal cannula to maintain higher than 90% saturation. The patients will be monitored every 5 min. Participants will be instructed to maintain aerobic activities on days that they are not performing the supervised PR program. Strength training for lower and upper limb muscles will be performed through a program consisting of 3 sets of 12 repetitions, initially using 60% of 1 maximal repetition (1RM), and this load will be increased to 70% by the 5th week and 80% in the 8th week of training [20]. For the upper limbs the training will be directed to the biceps, triceps, pectoral, and deltoid muscles, and for the lower limbs, the training will be for quadriceps and triceps femoris [3]. Guidance in energy conservation techniques as well as educational speeches regarding self-management of the disease will be provided [13]. The PRWIMT group will perform PR and IMT without any load; the PRIMTLL group will perform PR and IMT with a linear load; the PRIMTIVH group will perform PR and IMT with isocapnic voluntary hyperpnea.

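### The stated 95% power comes from a rehabilitation-versus-control study, but all three arms here receive rehabilitation, so it was not derived for any between-arm comparison in this trial

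*Protocol article*

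**What the plan says.** The Sample size section of the protocol article plans on six-minute walk distance. It states the error rates as "A two-tailed alpha error of 0.01 was implemented with a power of 95" per cent and gives the basis for the target as "considering clinical improvement for COPD patients after PR and a difference of 30 m between groups on the walking test". It then says that the "means and standard deviations of the time observed in the 6MWT in the rehabilitation and control groups were used". The values are 312.43 (SD 51.26) to 342.85 (SD 48.82) m for the rehabilitation group and 305.13 (SD 54.60) to 298.20 (SD 52.81) m for the control group. From these it reports an effect size of 1.04 and 32 subjects.

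The 32 are assigned to the two active IMT arms together, 16 each. Sixteen more are added as the control arm, making 48, and the total is raised to 60 for attrition.

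The Intervention section says: "All three groups will submit to a conventional rehabilitation program consisting of aerobic exercise on a treadmill". For the arm that serves as control, the PRWIMT section says: "The PRWIMT protocol consists of conventional PR as previously described". That arm also receives IMT with no load, as placebo. The Statistics analysis section compares the three groups by two-way ANOVA with Bonferroni post hoc tests at 0.05.

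**The concern.** The source study contrasts rehabilitation with control. The Sample size section carries its rehabilitation group over to the two IMT arms and its control group over to PRWIMT. But PRWIMT is itself a rehabilitation arm, so the comparisons the trial will make concern what IMT adds to PR and which IMT mode does better. The article gives no expected difference for either. Its Background section cites studies in which IMT did not improve exercise performance.

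The stated power affects how the results will be read. The article says the trial will guide therapists to the most effective type of training. A reader who believes the trial has 95% power would take a non-significant contrast as evidence that IMT adds nothing, or that the two modes are equivalent. If the real power is much lower, neither reading is justified.

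**Working it through.** **Inputs.** Means, SDs, alpha 0.01 (two-sided), power 95%, effect size 1.04, 30 m and 16 per arm are all from the Sample size section. The pre-post correlation r is not given, so it is assumed and varied.

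**1. The plan's own figure.** For d = 1.04, two-sided alpha 0.01 and 95% power:

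n per group = 2(2.576 + 1.645)² / 1.04² = 2 × 17.82 / 1.0816 ≈ 32.9, so 33 (35 by the t-test).

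The 32 is thus close to a per-group number, but the plan spreads it over two arms. As a total for two groups the same formula gives 66, not 32. This is a related but separate problem.

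**2. The difference in the inputs.**
- Rehabilitation group, change: 342.85 − 312.43 = 30.42 m
- Control group, change: 298.20 − 305.13 = −6.93 m
- Between groups, in change: 30.42 + 6.93 = 37.35 m
- Between groups, after treatment: 342.85 − 298.20 = 44.65 m

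The stated 30 m between groups is neither 37.35 nor 44.65 m. It nearly equals the gain within the source rehabilitation group.

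**3. Where 1.04 could come from.** The pooled SD of the four values is √[(51.26² + 48.82² + 54.60² + 52.81²)/4] = 51.9 m, and the SD of change is about 51.9 × √[2(1 − r)].
- On 37.35 m, d = 1.04 needs an SD of change of 37.35/1.04 = 35.9 m, which is r of about 0.76.
- On 30 m, it needs 30/1.04 = 28.8 m, which is r of about 0.85.

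Either is possible. Neither correlation is stated.

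**4. Power at 16 per arm.** Two-sample t-test on change, noncentral t. The 0.05/3 column assumes Bonferroni over the three pairwise contrasts.

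| True effect | alpha 0.01 | 0.05/3 | 0.05 |
|---|---|---|---|
| d = 1.04 (plan's value) | 58% | 66% | 81% |
| 30 m, r = 0.5 (SD of change 51.9 m, d = 0.58) | 15% | 20% | 35% |
| 30 m, r = 0.8 (SD 32.9 m, d = 0.91) | 45% | 53% | 70% |
| 30 m, r = 0.9 (SD 23.3 m, d = 1.29) | 81% | 86% | 94% |

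Pooling the two IMT arms against control (32 v 16) at d = 1.04 gives 76% at alpha 0.01.

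**5. If the increment from IMT is smaller than the borrowed effect.** The documents give no figure, so fractions of 1.04 are assumed. At 75%, 50% and 25% (d = 0.78, 0.52, 0.26), power at alpha 0.01 with 16 per arm is 31%, 12% and 3%.

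**6. Precision.** The half-width of the unadjusted 95% interval for a pairwise difference at 16 per arm is t(30 df) × SD of change × √(2/16). For r = 0.5 this is 2.042 × 51.9 × 0.354 = 37.5 m. For r = 0.8 it is 2.042 × 32.9 × 0.354 = 23.8 m. The target is 30 m.

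**The case against.** The strongest defence is that 30 m can be read as a minimum important difference, since the text speaks of clinical improvement. Such a target could be set for an IMT contrast whatever study supplied the SDs. That is fair as far as it goes, and the fix allows for it. But the section says that the rehabilitation and control means were used in the calculation, and it does not justify 30 m as a difference between PR with and without IMT. At 16 per arm, 30 m also misses 95% power at alpha 0.01 throughout the correlation range examined.

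A second defence concerns the effect size. A reader might divide 30 m by the printed SDs, obtain 0.58, and conclude that 1.04 is simply wrong. The documents do not support that. The calculation is described as a repeated-measures ANOVA, for which the SD of change matters, and 37.35 m gives 1.04 at a correlation of about 0.76. The figure cannot be verified, but it is not refuted. With two groups and two time points, the group-by-time test is the same as a t-test on change, so if 1.04 is a standardised difference in change, the 58% still applies.

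Two other inferences go too far. The article calls the source comparator only a control group. That it had no rehabilitation is suggested by the labels and by its decline, but is not stated. Nor is there ground for saying that the comparison of the two IMT modes has still less power: the arms are equal in size, so power for the same difference is the same, and no expected difference between modes is given.

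**Conclusion.** The point holds. The 95% power and the effect size of 1.04 rest on a rehabilitation-versus-control contrast that no pair of arms in this trial reproduces. The target of 30 m does not match the inputs listed beside it.

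On the plan's own effect size, 16 per arm gives 58% power at its own alpha of 0.01, and 81% even at an unadjusted 0.05. For a true 30 m difference in change, power at alpha 0.01 runs from 15% to 81% over assumed correlations of 0.5 to 0.9. All these figures assume a t-test on change, equal SDs in the arms and 16 analysed per arm.

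The 30 m figures depend on the unstated correlation. They show that the 95% is unsupported, and none of them should be taken as the trial's actual power. They also reflect the small number per arm as well as the borrowed contrast. The cost of the borrowed contrast alone cannot be fixed, because the article gives no expected increment for IMT; the fractions in step 5 only illustrate it.

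**What to change.** In the Sample size section:

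- Withdraw the 95% power claim for the between-arm comparisons.
- State the target as a between-arm difference in change in six-minute walk distance for IMT added to PR. If 30 m is kept, justify it as a minimum important difference for that contrast.
- Give the sponsor's own SD of change, or the correlation behind it, with its source.
- State 16 per arm and the Bonferroni-adjusted alpha that the analysis will use, so that this section and the Statistics analysis section agree.
- Report the resulting, lower power at the fixed sample size.

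In the analysis and discussion text, say that pairwise differences will be reported with confidence intervals, and that a non-significant contrast will not be read as no added benefit or as equal effectiveness.

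The cost is rewording and a less favourable stated power. No extra patients and no change to treatment are needed.
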